#### Translational research

All participants will be asked to provide separate informed consent for collection of blood samples and/or tumour tissue for future translational research. If patients give such consent, an additional 20 ml blood will be drawn during regular blood draws before the start of induction chemotherapy (experimental arm only), before chemoradiotherapy, before surgery, 3 months after surgery, and once a year during 3 years of follow-up, resulting in seven samples per patient in the experimental arm and six per patient in the control arm. Tumour tissue will be collected by the pathologist, fresh frozen and stored until further use.

#### Central multidisciplinary team meetings

During the study inclusion period, a monthly central MDT meeting will be organized for quality control. All newly included patients will be discussed during this meeting, which has been designed as a teleconference. In addition, eligible patients will be discussed in the event of uncertainty about whether they meet the inclusion and/or exclusion criteria. Patients who are under treatment at the time of the central MDT meeting, or who have completed treatment, will be discussed only if there are remarkable findings, such as progression of disease resulting in unresectability.

### Outcomes

The primary outcome of the study is the proportion of patients with a clear resection margin. A resection margin is considered clear (R0), if there are no tumour cells in any of the resection surfaces as determined by microscopy (resection margin more than 0 mm).

Secondary outcomes are:

3- and 5-year local re-recurrence-free survival, defined as the interval between surgery and local re-recurrence;3- and 5-year progression-free survival, defined as the interval between randomization and progression of local recurrence, local re-recurrence, distant metastases or death;3- and 5-year metastasis-free survival, defined as the interval between randomization and development of distant metastases;3- and 5-year disease-free survival, defined as the interval between surgery and local re-recurrence, distant metastases or death;3- and 5-year overall survival, defined as the interval between randomization and death;pathological response, graded according to the Mandard grading system^40^;radiological response, scored according to the magnetic resonance tumour regression grade (mrTRG);compliance rate with induction chemotherapy (i.e., the number of patients receiving CAPOX, FOLFOX or FOLFIRI as initial regimen will be tabulated, and dose modification and reason will be summarized for each regimen);toxicity of induction chemotherapy, scored from day 1 of the first cycle of induction chemotherapy until 1 month after the final administration, and graded according to the Common Terminology Criteria for Adverse Events (CTCAE) version 5.0;compliance rate with chemoradiotherapy, calculated as the total radiotherapy dose received divided by the total planned dose;toxicity of chemoradiotherapy, scored from start of radiotherapy until 3 months after the final dose of radiotherapy, and graded according to CTCAE version 5.0;number of patients undergoing surgery;surgical characteristics (e.g., type of resection, ostomy, use of intraoperative radiotherapy, blood loss, duration of operation, intraoperative complications);major surgical morbidity rate scored from the date of surgery to 3 months after surgery, and graded according to the Clavien–Dindo classification^41^;quality of life, assessed with EQ-5D-5L™, QLQ-C30 and QLQ-CR29 questionnaires at inclusion, and at 3 and 12 months after surgery; andcost-effectiveness and cost–utility, based on Dutch costing guidelines for healthcare, the case report forms, and the EQ-5D-5L™ questionnaire.

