**Assessments**					
Baseline characteristics	☒				
Toxicity of chemoradiotherapy		☒			
Radiological response		☒			
Pathological response			☒		
Surgical characteristics			☒		
Postoperative morbidity			☒		
Progression-free survival				☒^#^	☒^§^
Local recurrence-free survival				☒^#^	☒^§^
Disease-free survival				☒^#^	☒^§^
Overall survival				☒^#^	☒^§^
Quality of life	☒			☒^¶^	
Costs	☒			☒^¶^	

* 4 to 6 weeks after finishing chemoradiotherapy;

† after finishing chemoradiotherapy and before surgery;

‡ 3 months after surgery;

§ 6-monthly;

¶ 3 and 12 months after surgery;

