#### Induction chemotherapy

Patients allocated to the experimental arm will start treatment with induction chemotherapy within 4 weeks after randomization. Induction chemotherapy will consist of either three 3-week cycles of CAPOX (oxaliplatin 130 mg per m^2^ body-surface area (BSA) intravenously (i.v.) on day 1, capecitabine 1000 mg per m^2^ BSA, orally, twice daily on days 1–14), four 2-week cycles of FOLFOX (85 mg per m^2^ BSA of oxaliplatin i.v. on day 1, 400 mg per m^2^ BSA of leucovorin i.v. on day 1, 400 mg per m^2^ BSA of bolus 5-fluorouracil i.v. on day 1 followed by 2400 mg per m^2^ BSA of continuous 5-fluorouracil i.v. on days 1–2), or four 2-week cycles of FOLFIRI (180 mg per m^2^ BSA of irinotecan i.v. on day 1, 400 mg per m^2^ BSA of leucovorin i.v. on day 1, 400 mg per m^2^ BSA of bolus 5-fluorouracil i.v. on day 1 followed by 2400 mg per m^2^ BSA of continuous 5-fluorouracil i.v. on days 1–2). The choice of chemotherapy agent will be left to the physician’s discretion.

After three cycles of CAPOX or four cycles of FOLFOX or FOLFIRI, pelvic MRI will be performed for local restaging, and high-dose thoracoabdominal CT for restaging of possible distant metastases. Restaging imaging will be discussed during a dedicated MDT meeting in one of the expert centres. If a patient develops distant metastases or local disease becomes unresectable, best palliative treatment will be offered according to the standard of care. If a patient has progressive local disease, but surgery is still considered feasible, no further systemic therapy will be administered and patients will start treatment with chemoradiotherapy. If a patient has stable or responsive disease, induction chemotherapy will be continued with either one 3-week cycle of CAPOX or two 2-week cycles of FOLFOX or FOLFIRI.

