#### Chemoradiotherapy

Patients in the experimental arm will start chemoradiotherapy within 3–5 weeks after the first day of the last cycle of chemotherapy. Patients in the control arm will start chemoradiotherapy within 4 weeks after randomization. The radiotherapy dose will depend on whether the patient received radiotherapy previously. In radiotherapy-naive patients, full-course radiotherapy will consist of 25 × 2.0 Gy or 28 × 1.8 Gy radiotherapy. In patients with a history of radiotherapy, the radiotherapy dose will consist of 15 × 2.0 Gy. The target volume will be defined by the gross, clinical, and planning target volumes (GTV, CTV and PTV respectively), and will be similar for radiotherapy-naive and previously irradiated patients. The GTV contains all macroscopic visible tumour, the CTV includes the GTV with a margin of 1 cm, without adjustment of the CTV towards other organs, and the PTV includes the CTV with a margin that can be determined according to local policy. Concomitant chemotherapy will comprise capecitabine, administered orally at a dose of 825 mg/m^2^ twice daily on radiotherapy days. In the event of unacceptable toxicity caused by capecitabine during induction chemotherapy, concomitant tegafur/gimeracil/oteracil administered orally at a dose of 25 mg/m^2^ twice daily on radiotherapy days may be prescribed at the physician’s discretion.

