#### Restaging

Four to 6 weeks after the last day of radiotherapy, pelvic MRI will be performed for local restaging and high-dose thoracoabdominal CT for restaging of possible distant metastases. Restaging imaging will be discussed during a dedicated MDT meeting in one of the expert centres. In the event of distant metastases or unresectable local disease, best palliative treatment will be offered. Patients with resectable disease will undergo surgery.

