### Statistical methods

Demographics, patient, and tumour characteristics will be presented for each treatment arm. Continuous data will be reported as mean (standard deviation) or median (interquartile range or 95 per cent confidence interval), depending on the distribution. Categorical data will be reported as count with percentage. All statistical tests will be two-sided and *P* < 0.050 will be classified as statistically significant. Patients initially randomized but considered ineligible afterwards, based on information that should have been available before randomization, will be excluded from all analyses.

Analysis of the primary endpoint of this study, the proportion of patients with an R0 resection, will be based on the intention-to-treat principle using Fisher’s exact test. In addition, a per-protocol analysis will be performed as a sensitivity analysis.

All survival curves will be constructed according to the Kaplan–Meier method, and the log rank test will be used to compare treatment arms, adjusting for stratification factors at randomisation (previous radiotherapy, previous systemic therapy, and expert centre). In addition, hazard ratios will be calculated using a Cox proportional hazards regression model, adjusting for stratification factors. Metastasis-free survival, progression-free survival, and overall survival will be based on the intention-to-treat group. Local re-recurrence free survival and disease-free survival analyses will include only patients who underwent surgery.

Data on surgical characteristics, histopathological characteristics, and major surgical morbidity will be presented by treatment arm, and will be derived only for patients who underwent surgery. The number of patients undergoing surgery will be analysed in the intention-to-treat population. Comparison between treatment arms will be done by means of Fisher’s exact test.

The absolute and relative incidence of toxicities related to the administration of induction chemotherapy or chemoradiotherapy will be presented by treatment arm, and analysed in all patients who received at least one dose of neoadjuvant chemotherapy (experimental arm) or chemoradiotherapy (control arm). Comparison between treatment arms will be done by means of Fisher’s exact test.

Comparison of health-related quality of life between the two treatment arms at baseline and over time will be performed by means of a random-effects regression model and will be based on the intention-to-treat group.

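### Progression-free survival counts pre-surgery local growth even when the tumour stays resectable, and the experimental arm has one more restaging than the control arm at which such growth can be recorded

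*Protocol article*

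**What the plan says.** Under Outcomes, PFS is "3- and 5-year progression-free survival, defined as the interval between randomization and progression of local recurrence, local re-recurrence, distant metastases or death". Growth of the existing recurrence is listed separately from re-recurrence after surgery, so the first item can only mean growth of a tumour not yet resected. Nothing limits it to growth that makes the tumour unresectable.

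The section on induction chemotherapy adds a restaging in the experimental arm: "After three cycles of CAPOX or four cycles of FOLFOX or FOLFIRI, pelvic MRI will be performed for local restaging". CT is done at the same time. For one group the curative plan goes on: "If a patient has progressive local disease, but surgery is still considered feasible, no further systemic therapy will be administered", and these patients move to chemoradiotherapy.

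The Restaging section applies to both arms: "Four to 6 weeks after the last day of radiotherapy, pelvic MRI will be performed for local restaging". Patients who are still resectable then have surgery. In Table 2 this scan, "4 to 6 weeks after finishing chemoradiotherapy", is the control arm's only pelvic MRI between baseline and surgery.

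Statistical methods fixes the analysis set: "Metastasis-free survival, progression-free survival, and overall survival will be based on the intention-to-treat group". The comparison is by log-rank test and Cox model, both adjusted for the stratification factors.

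**The concern.** A patient in the experimental arm whose tumour has grown at the mid-induction MRI, but who then has chemoradiotherapy, an R0 resection and five disease-free years, has a PFS event at the date of that MRI. A control patient whose tumour grows by the same amount before or early in chemoradiotherapy and then shrinks has no scan at that point, and so no event. To that extent the event depends on an extra look in one arm, and it does not mark failure of the curative plan.

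PFS matters here because it is the only time-to-event outcome analysed by intention to treat that includes local control. Local re-recurrence-free and disease-free survival start at surgery and include only operated patients. Metastasis-free and overall survival have no local component.

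**Working it through.** **The plan's own figure.** No figure is given for PFS. The only stated calculation is for R0: 45% against 60%, two-sided 5%, 80% power. With a mean proportion of 0.525, n = [1.960·√(2·0.525·0.475) + 0.842·√(0.45·0.55 + 0.60·0.40)]² / 0.15² = 172.8, or 173 per arm, and 346/0.95 = 364.2. The stated 173 and 364 are reproduced, and nothing below touches them.

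**When the scans fall (weeks from randomization).** First treatment starts within 4 weeks in both arms. For the control arm: "Patients in the control arm will start chemoradiotherapy within 4 weeks after randomization". Assuming five fractions a week, radiotherapy lasts 3 weeks (15 fractions), 5 weeks (25) or 5.6 weeks (28).

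- Mid-induction MRI: earliest 0 + 4×2 = 8; latest 4 + 3×3 = 13.
- Control MRI after chemoradiotherapy: earliest 0 + 3 + 4 = 7; latest 4 + 5.6 + 6 = 15.6.
- With the latest permitted start (week 4): mid-induction MRI at 12–13, control MRI at 11–15.6.
- Experimental MRI after chemoradiotherapy, latest start and full induction: 23–30.6.

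So there are two pre-surgery restagings against one, but the first look comes at about the same time in both arms.

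**When surgery falls.** In the experimental arm, "Patients in the experimental arm will start chemoradiotherapy within 3–5 weeks after the first day of the last cycle of chemotherapy". With the latest start and full induction, the last CAPOX cycle begins at week 4 + 9 = 13 and the last FOLFOX or FOLFIRI cycle at week 4 + 10 = 14. Chemoradiotherapy then starts at weeks 16–18 or 17–19, against week 4 in controls, which is 12–15 weeks later. Surgery is timed from the end of chemoradiotherapy in both arms (weeks 29–38.6 against 17–23.6), and follow-up CT is timed from surgery. The delay therefore carries through to every follow-up scan.

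**Size, with no true treatment effect.** The share g of the experimental arm with resectable growth at mid-induction is not in the documents, so 5%, 10% and 15% are assumed. No counterpart growth is counted in controls. The hazard ratio is the log-rank ratio (O/E experimental)/(O/E control) over 5 years.

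*Model A: continuous time, exponential PFS identical in both arms, true 3-year PFS 30/40/50%, share g given an event at week 13.*

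- g = 5%: HR 1.05/1.06/1.07
- g = 10%: HR 1.11/1.13/1.15
- g = 15%: HR 1.17/1.19/1.22

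*Model B: same null, but events are detected only at the scheduled scans, with median PFS assumed at 12/18/24/36 months.*

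| g | HR (experimental/control) | 3-year PFS difference, experimental minus control (points) |
|---|---|---|
| 0 | 1.01/1.01/1.01/1.03 | +2.7/+3.3/+3.4/+2.8 |
| 5% | 1.07/1.07/1.09/1.10 | +1.8/+1.9/+1.3/+0.2 |
| 10% | 1.13/1.13/1.15/1.19 | +0.8/+0.3/−0.5/−2.3 |
| 15% | 1.19/1.20/1.23/1.28 | 0.0/−1.1/−3.0/−5.3 |

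Model A ignores scan timing and gives a fall of 1.5 to 2.5 points in 3-year PFS at g = 5%. Model B, which follows the protocol's schedule, gives a small gain at the same g, because later follow-up scans delay detection in the experimental arm. The hazard ratio leans the same way in both models; the 3-year difference does not.

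**The case against.** A reader might infer that only experimental patients can have an early PFS event while completing curative treatment, and that PFS is therefore biased against induction. The documents do not support that much.

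- Resectable growth on the control arm's MRI after chemoradiotherapy is an event under the same wording, at a similar time from randomization. What is confined to one arm is growth seen before radiotherapy.
- At that time control patients have had chemoradiotherapy and experimental patients have not. Some excess growth may be a true effect of deferring it; the article's section on benefits and disadvantages names progression during prolonged neoadjuvant treatment as a risk. Leaving it out altogether would hide part of what is being tested.
- The direction for 3-year PFS is not settled, as Model B shows. The same timing argument applies at 5 years, where no rate was calculated.
- The shares of 5–15% have no source in the documents, and the models put no such events in the control arm.
- Counting any progression is conventional for PFS.

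All of this stands, and it narrows the point. It does not remove it: the extra look before radiotherapy remains, and the definition still treats a patient whose curative plan continues as a failure.

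It can also be said that no text links the mid-induction MRI to PFS, since Table 1 ticks PFS only under follow-up and lists radiological response under induction. This is weak, because overall survival is ticked in the same way although it too runs from randomization. The full protocol or SAP may hold detailed progression criteria, but the definition printed here has no exception.

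**Conclusion.** The point holds in a limited form. As written, local growth before surgery is a PFS event even when the disease stays resectable and treatment with curative intent continues. Growth seen before radiotherapy can be recorded only in the experimental arm.

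Under the null, the hazard ratio leans against induction: about 1.05–1.10 at an assumed 5% and 1.11–1.19 at an assumed 10%, taking both models together. These are upper values, because no counterpart growth is counted in controls and because early progressors would be likely to do worse than average in any case. No direction can be claimed for the 3- or 5-year rates. PFS is a secondary outcome, so this is an inexpensive improvement to its definition and no threat to the trial's main result.

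**What to change.** Before outcome data are seen, which matters in an open-label trial, pre-specify a second PFS analysis applied identically in both arms. In it, local progression before surgery is an event only if the multidisciplinary team judges the disease unresectable or curative treatment ends. Report it beside the present any-progression definition. Also report mid-induction growth in patients who continue curative treatment as radiological response.

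The cost is one sentence in the outcome definition and one extra analysis. No scan, visit or treatment changes, because resectability is already judged at each restaging. The added measure is closer to event-free survival and less comparable with trials that count any growth, which is why the present definition should stay alongside it.

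The second analysis does not remove the effect of timing follow-up scans from surgery: with g = 0, Model B still shows about 3 points at 3 years in favour of induction. The 3- and 5-year rates should be read with that in mind under either definition.

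### Metastasis-free and local re-recurrence-free survival leave out death but are planned as Kaplan–Meier curves, so their 3- and 5-year percentages will be biased

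*Protocol article*

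**What the plan says.** The Outcomes section lists five time-to-event secondary endpoints. Two of them end at a single disease event:

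- "3- and 5-year metastasis-free survival, defined as the interval between randomization and development of distant metastases"
- "3- and 5-year local re-recurrence-free survival, defined as the interval between surgery and local re-recurrence"

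Two others in the same list name death as an event. Progression-free survival is "defined as the interval between randomization and progression of local recurrence, local re-recurrence, distant metastases or death", and disease-free survival is "defined as the interval between surgery and local re-recurrence, distant metastases or death". The fifth is overall survival.

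Statistical methods then fixes one approach for all of them: "All survival curves will be constructed according to the Kaplan–Meier method, and the log rank test will be used to compare treatment arms". It adds that "hazard ratios will be calculated using a Cox proportional hazards regression model, adjusting for stratification factors". On populations it says "Metastasis-free survival, progression-free survival, and overall survival will be based on the intention-to-treat group", while local re-recurrence-free and disease-free survival are restricted to operated patients. It names no competing-risk method and states no rule for patients who die before the event of interest.

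**The concern.** Death is named where it is meant to count, so its absence from the other two definitions reads as deliberate. With those definitions, a patient who dies without metastasis (or re-recurrence) can enter a Kaplan–Meier analysis only as censored, that is, as if the event could still occur later. The resulting 3- and 5-year values answer neither of the questions that a reader would ask:

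- As the proportion alive and free of the event, which is what the word survival suggests, they are too high, because the dead are not failures.
- As one minus the probability of metastasis or re-recurrence, they are too low. Put the other way, one minus Kaplan–Meier is too high as a cumulative incidence.

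The endpoints are named by their 3- and 5-year values, so the affected numbers are the ones that will be reported and compared with other series. Deaths are not rare in this disease, so the discrepancy cannot be assumed negligible.

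**Working it through.** **Is there a stated figure to reproduce?** The article gives none for these two endpoints. Its sample size (173 per arm, 364 in total) rests on R0 rates of 45% and 60% and does not involve them.

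**How common is death?** The Introduction cites 5-year survival of 48–58% after R0 and 10–18% after R1/2 resection. Sample size gives about 60% R0 among operated patients. Hence 5-year survival of operated patients is:

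- low: 0.6 × 48% + 0.4 × 10% = 32.8%
- high: 0.6 × 58% + 0.4 × 18% = 42.0%

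So about 58–67% of operated patients would die within 5 years. These are deaths from all causes. Those that follow metastasis or re-recurrence do not compete with that endpoint, and the article does not give the split.

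**Assumptions for the size (not in the article).** Constant cause-specific hazards h_e (event) and h_d (death without the event). The 5-year Kaplan–Meier value with deaths censored is 50–70%. The net 5-year risk of death without the event is 10–40%.

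**Formulas at time t:**

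- Kaplan–Meier with deaths censored: KM = exp(−h_e·t)
- alive and event-free: EFS = exp(−(h_e + h_d)·t)
- cumulative incidence: CIF = h_e/(h_e + h_d) × (1 − EFS)

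**Worked example, 5 years, KM 60%, death risk 20%:**

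- h_e = −ln(0.60)/5 = 0.1022 per year; h_d = −ln(0.80)/5 = 0.0446 per year
- EFS = 0.60 × 0.80 = 48.0%, so KM is 12.0 points too high as alive and event-free
- CIF = 0.1022/0.1468 × 0.52 = 36.2%, against 1 − KM = 40.0%, so 3.8 points too high

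**All 5-year results.** Each cell gives KM minus EFS, then (1 − KM) minus CIF, in percentage points.

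| KM at 5 years | Death risk 10% | 20% | 30% | 40% |
|---|---|---|---|---|
| 50% | 5.0; 2.3 | 10.0; 4.6 | 15.0; 7.1 | 20.0; 9.7 |
| 60% | 6.0; 1.9 | 12.0; 3.8 | 18.0; 5.8 | 24.0; 8.0 |
| 70% | 7.0; 1.4 | 14.0; 2.9 | 21.0; 4.5 | 28.0; 6.2 |

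At 3 years the same assumptions give about 4–21 points and 1–4 points.

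The grid is an illustration and is not calibrated to the cited survival. The proportion alive and event-free cannot exceed overall survival, so cells whose EFS is above 42.0% (the worked example among them) would not fit operated patients with the cited 5-year survival. The full range is kept because the trial's own mortality is unknown.

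**The case against.** **Censoring is inferred.** The article nowhere says in words that deaths are censored, it condenses a fuller protocol, and censoring rules are commonly left to an analysis plan. That is fair as to wording. But the article fixes both the event definitions and the estimator, and together they leave no other treatment of a death. An analysis plan that counted death would change the stated definition, and one that used a competing-risk estimator would depart from the stated method.

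**The comparison of arms is not spoiled.** This stands. As far as the handling of death goes, the log rank test and Cox model with deaths censored are valid comparisons of cause-specific hazards. The fault is confined to the absolute percentages and the survival label.

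**Harm is not hidden.** A reader might infer that toxic or postoperative deaths in the more intensive arm would disappear from view. The article does not support that. Overall and progression-free survival count deaths from randomization by intention to treat, and disease-free survival counts them after surgery. Serious adverse events are recorded from randomization, and a safety board reviews major morbidity. Deaths before surgery never enter the re-recurrence analysis at all, so adding death to that endpoint would not capture them.

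**Larger errors are not established.** A reader might also take the 70–80% re-recurrence rate from the Introduction. A 5-year Kaplan–Meier risk of 75% with assumed death hazards of 0.10–0.20 per year gives a true incidence of about 62–53%, an error of 13–22 points. That rate is cited for incomplete resections only, whereas the endpoint covers all operated patients, about 60% of them R0. Those figures do not describe the planned endpoint.

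**Conclusion.** The point holds for the absolute 3- and 5-year rates of two secondary endpoints and for their names. Followed as written, the Kaplan–Meier values overstate the proportion alive and event-free, and their complements overstate cumulative incidence. The direction of both errors follows from the definitions and needs only that some patients die first. The size does not follow from the article. About 5–28 points and 1–10 points at 5 years rest on constant hazards and on the assumed ranges above. The cited all-cause survival makes competing deaths plausible but does not measure them. The primary endpoint, the planned 364 patients, and overall, progression-free and disease-free survival are untouched.

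**What to change.** Choose one of two routes for both endpoints and state it in the protocol and analysis plan:

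1. Keep the names and add death from any cause as an event, in line with progression-free and disease-free survival. Kaplan–Meier, log rank and Cox can then stay as planned.
2. Keep the events and rename the endpoints time to distant metastasis and time to local re-recurrence. Report 3- and 5-year Aalen–Johansen cumulative incidence with death as a competing event, and label the Cox results cause-specific hazard ratios.

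Either route is a change of wording and analysis only, since dates of death are already needed for overall survival. The cost of the first is that the reported survival percentages fall, possibly by 10 points or more at 5 years, and are no longer comparable with series that censor deaths. The second leaves the event definitions as they are but gives up the survival label.
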